### Termination Criteria

In this study, patients who experience severe adverse reactions or develop severe issues during the trial (eg, sudden exacerbation of preexisting conditions or new severe diseases) that make it impossible to assess efficacy will be advised to discontinue the trial.

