### Elimination Criteria

Participants who do not adhere to the study requirements during the trial, and those who do not meet the inclusion criteria after enrollment, will be removed from this study.

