### Dropout Criteria

In this study, the dropout criteria include the following: (1) participants who meet the inclusion criteria but do not complete the trial or who withdraw midway for various reasons; (2) participants who do not follow the prescribed treatment plan or who receive other treatments or medications that interfere with the assessment of efficacy; and (3) participants who are lost to follow-up or die before completing the trial.

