**Figure 1 figure1:**
[figure not shown]
Flow diagram of the trial procedure. ABPM: ambulatory blood pressure monitoring; FBG: fasting blood glucose; FINS: fasting insulin; HbA1c: glycated hemoglobin; HDL: high-density lipoprotein; LDL: low-density lipoprotein; TC: total cholesterol; MoCA: Montreal Cognitive Assessment.

**Table 1 table1:** Time points of the outcome measures.

Assessment	Enrollment and baseline	Allocation		After allocation						Closeout
		0 wk	2 wk	4 wk	6 wk	8 wk	10 wk	12 wk	24 wk	
Informed consent	✓	—^a^	—	—	—	—	—	—	—	—
Inclusion or exclusion	✓	—	—	—	—	—	—	—	—	—
General information	✓	—	—	—	—	—	—	—	—	—
Random allocation		✓	—	—	—	—	—	—	—	—
Intervention	—	✓	✓	✓	✓	✓	✓	✓		—
Concomitant medication	✓	—	✓	✓	✓	✓	✓	✓	✓	—
24 h ABPM^b^	✓	—	—	✓	—	—	—	✓	✓	—
24 h Holter ECG^c^	✓	—	—	✓	—	—	—	✓	✓	—
Lipid profile (Triglycerides, TC^d^, HDL^e^, and LDL^f^)	✓	—	—	✓	—	—	—	✓	✓	—
Glycemic markers (FPG^g^, FINS^h^, HbA_1c_^i^)	✓	—	—	—	—	—	—	✓	✓	—
^Hepatic and renal function^	✓	—	—	—	—	—	—	✓	✓	—
^Phlegm-damp constitution^	✓	—	—	—	—	—	—	✓	✓	—
Cardiovascular risk stratification	✓	—	—	—	—	—	—	✓	✓	—
MoCA^j^	✓	—	—	—	—	—	—	✓	✓	—
Adverse events and other unintended effects	—	—	✓	✓	✓	✓	✓	✓	✓	—
^Compliance monitoring^	—	—	✓	✓	✓	✓	✓	✓	✓	—
^Completion summary^	—	—	✓	✓	✓	✓	✓	✓	✓	—

^a^Not available.

^b^ABPM: ambulatory blood pressure monitoring.

^c^Holter ECG: Holter electrocardiogram.

^d^TC: total cholesterol.

^e^HDL: high-density lipoprotein.

^f^LDL: low-density lipoprotein.

^g^FBG: fasting blood glucose.

^h^FINS: fasting insulin.

^i^HbA_1c_: glycated hemoglobin.

^j^MoCA: Montreal Cognitive Assessment.

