#### Safety Evaluation

Major adverse cardiovascular and cerebrovascular events, liver function (alanine aminotransferase and aspartate aminotransferase) and kidney function (blood urea nitrogen and creatinine) and moxibustion-related adverse events (burns, blisters, dizziness during moxibustion, ulceration, infection, and local abscesses at the moxibustion site; other discomforts after moxibustion may include dizziness, fatigue, allergies, and loss of appetite) will be recorded in this study. Moreover, adverse events will be monitored through patient self-reports and assessments by health care professionals during the study. Participants will be instructed to immediately report any adverse events to their supervising clinician, who will determine whether further examinations or treatments are necessary and will provide timely interventions. For serious adverse events, the trial will be immediately halted. All adverse reactions, their severity, duration, and any actions taken will be thoroughly documented.

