### Statistical Analysis

Data analysis of the primary outcome will be based on the full analysis set constructed by the intention-to-treat principle, whereby patients will remain in their original group regardless of contamination. The per-protocol set will also be analyzed using sensitivity analysis for the primary outcome to evaluate whether contamination affects the direction of the effect. The secondary outcomes will also be compared based on the per-protocol set. The need to impute missing values will be determined by the proportion of and reasons for missing data. If imputation is necessary, appropriate methods, such as the last observation carried forward, the “best-worst-case” scenario, and multiple imputation regression modeling, will be chosen according to the distribution of the missing values.

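### The harm-based stopping rule advises leaving the trial rather than stopping moxibustion, and the neighbouring rules class off-treatment patients as removed or dropped out, which fits badly with the intention-to-treat analysis

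*Protocol article*

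**What the plan says.** Four sections of the protocol article bear on the point.

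- **Termination Criteria.** Patients with severe adverse reactions or severe new problems "that make it impossible to assess efficacy will be advised to discontinue the trial". No other action is given.
- **Elimination Criteria.** The rule on removal, which covers two kinds of patient, reads: "do not adhere to the study requirements during the trial, and those who do not meet the inclusion criteria after enrollment, will be removed".
- **Dropout Criteria.** Item 1 covers "participants who meet the inclusion criteria but do not complete the trial or who withdraw midway for various reasons". Item 2 covers "participants who do not follow the prescribed treatment plan" and those given other treatment that interferes with the efficacy assessment. Item 3 covers loss to follow-up and death.
- **Statistical Analysis.** The primary outcome is analysed on a full analysis set under intention to treat, "whereby patients will remain in their original group regardless of contamination". A per-protocol set serves as a sensitivity analysis. Whether and how to impute is decided later, from the amount of and reasons for missing data.

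On safety, Table 1 has a row for "Adverse events and other unintended effects" at every visit from week 2 to week 24. Safety Evaluation requires that "All adverse reactions, their severity, duration, and any actions taken will be thoroughly documented", and it counts liver and kidney function among the safety measures.

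**The concern.** Stopping a treatment and leaving a study are different events, and an intention-to-treat analysis depends on keeping them apart. A patient who can no longer safely use moxibustion can often still wear a blood pressure monitor at week 12 and give a blood sample. If the written instruction is to leave, those measurements are not taken.

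Two things are at stake. The primary outcome would be missing for a reason tied to harm, and the gap would pass to imputation choices that the article leaves open. The patients whose events most need follow-up would also miss their scheduled safety assessments.

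**Working it through.** No sample-size or power figure enters this point. The check sets the rules side by side and counts what Table 1 schedules after an exit.

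**Step 1: where each rule sends the patient.**

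| Patient | Rule that applies | Result |
|---|---|---|
| Severe harm that prevents efficacy assessment; takes the advice | Termination Criteria, then Dropout item 1 | Leaves; dropout |
| Stops moxibustion but keeps attending | Dropout item 2; Elimination Criteria if read literally | Dropout, possibly removed |
| Given interfering treatment, for example for an exacerbation | Dropout item 2 | Dropout |

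None of the three rules describes a patient who is off moxibustion but still followed. The sentence on intention to treat settles which group a patient is analysed in. It does not arrange for a measurement after treatment stops.

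**Step 2: inputs from Table 1.**

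- Adverse-event recording: weeks 2, 4, 6, 8, 10, 12, 24, so 7.
- Post-baseline ambulatory blood pressure monitoring (ABPM): weeks 4, 12, 24, so 3. Week 12 is the primary time point.
- Post-baseline liver and kidney tests: weeks 12, 24, so 2.

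**Step 3: scheduled assessments lost.** For a patient who leaves after completing the visit at week w, the loss is the number of scheduled weeks later than w.

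| Leaves after week | Adverse-event recordings lost | ABPM lost | Liver and kidney tests lost | Week-12 primary ABPM |
|---|---|---|---|---|
| 2 | 6 of 7 | 3 of 3 | 2 of 2 | lost |
| 4 | 5 of 7 | 2 of 3 | 2 of 2 | lost |
| 6 | 4 of 7 | 2 of 3 | 2 of 2 | lost |
| 8 | 3 of 7 | 2 of 3 | 2 of 2 | lost |
| 10 | 2 of 7 | 2 of 3 | 2 of 2 | lost |
| 12 | 1 of 7 | 1 of 3 | 1 of 2 | kept |

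An exit after any of the five visits before week 12 loses the primary measurement and both laboratory safety tests. Keeping only the week-12 and week-24 visits would recover the primary ABPM, both laboratory tests and 2 adverse-event recordings.

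**Step 4: what the counts do not include.** The Overview of Assessment and Outcomes has moxibustion adverse events and target organ injury recorded throughout the study period. Safety Evaluation adds patient self-report, immediate reporting to the supervising clinician, and further examinations where needed. These routes do not depend on the scheduled visits, so the safety columns above are upper bounds. The loss of the week-12 ABPM has no such substitute.

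**The case against.** The case against is substantial, and much of it stands.

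- **The trigger is narrow and the action is advice.** Termination Criteria covers only events that rule out an efficacy assessment. A reader might infer that any harm-based stop, such as a burn or blister, sends the patient out of the trial. The text does not say that.
- **Dropout is a label.** Dropout Criteria ends no visits and bars no data. A reader might infer that dropouts leave the full analysis set or that contact with them ends. The article says neither, and a patient measured at week 12 while off treatment fits the full analysis set. Only Elimination Criteria speaks of removal. Applying it to someone stopped on clinical advice is a literal reading that may not be intended.
- **Safety data have other routes.** A reader might take the visit counts as safety information lost outright. Event-driven reporting means that they are only a ceiling.
- **The article is condensed.** Off-treatment follow-up may be set out in a full protocol that is not shown. Silence alone would be no finding. Here, however, the article states an action (leave the trial) and two classifications (removed, dropout), and those are what work against the analysis.
- **A reading from such a patient may not inform efficacy.** That is the rule's own premise. Under intention to treat, though, the outcome of a patient stopped for harm belongs to the treatment comparison, so the premise does not justify giving up the measurement.

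A separate wording query lends no weight here. Safety Evaluation says "For serious adverse events, the trial will be immediately halted" without stating whether this means one participant's involvement or the whole study.

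**Conclusion.** The point holds as a minor design fault. Followed as written, the harm rule trades a treatment stop for a study exit, and the two neighbouring rules class off-treatment patients as dropouts or, read literally, remove them. For each patient who takes the advice before week 12, the cost is the primary ABPM and the scheduled week-12 and week-24 liver and kidney tests, plus up to 2 to 6 of the 7 scheduled adverse-event recordings, depending on when the patient leaves.

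This assumes that leaving the trial means no further scheduled visits, and that the patient accepts the advice. The article gives no rate of harm-based stops. A reader might infer that the primary result is biased, or biased in a particular direction. The documents support no such statement, because the number of affected patients and their split between the arms are unknown.

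**What to change.** **In the rules, where still applied or reused.** Reword Termination, Elimination and Dropout Criteria so that harm, non-adherence or interfering treatment leads at most to stopping moxibustion. State that consenting patients keep the week-12 and week-24 assessments and that adverse events are followed to resolution. Reserve study withdrawal for patients who withdraw consent or cannot be reached.

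**In this trial now.** The Results section reports data collection as ended in February 2025 (though it also describes the data as still in collection) and says that no analysis has been done. The analysis can therefore still keep every randomised patient's available data after stopping in the intention-to-treat analysis, whatever label the three sets of criteria gave them. The participant-flow report should show treatment stops for harm separately from study withdrawals.

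**Cost.** Wording in three short sections and one line in the participant flow. If the rule is reused, there are at most two off-treatment visits per affected patient. Visits already missed cannot be restored.

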### Recruitment

In this study, we disseminate study information through official social media, flyers, and online articles in hospitals and communities for patients’ reference. Interested patients can register online and based on proximity, visit designated clinical sites for screening. After confirmation by clinical physicians and after signing the informed consent form, eligible participants will be randomly assigned to a treatment group or a control group in a 1:1 ratio and will receive 12 weeks of moxibustion treatment, followed by 12 weeks of follow-up. All procedures will strictly adhere to the Declaration of Helsinki.

### Sample Size Calculation

The primary efficacy evaluation index for this study is the morning systolic blood pressure measured by 24-hour ambulatory blood pressure monitoring (ABPM). The sample size was estimated based on statistical methods. Preliminary trial data showed that the treatment group had a 7.2 (SD 3.3) mm Hg greater reduction in 24-hour morning systolic blood pressure than the control group. In this study, we apply the superiority design and set the superiority margin (Δ) as 5 mm Hg [22], with a significance level of α equal .025 (1-sided) and a power of β equal .1. The mean value for treatment improvement between the treatment and control groups is set at 7.2 (SD 3.3) mm Hg, with a SD (σ) of 3.3 mmHg, based on the formula for comparing means in a superiority trial [22]:

[figure not shown]

The primary efficacy endpoint of this study was the change in morning systolic blood pressure as measured by 24-hour ABPM. Sample size determination was based on a superiority design for comparing two independent means. The calculation incorporated the following parameters: an expected between-group difference (μ₁–μ₂) of 7.2 mm Hg derived from preliminary data, a common SD (σ) of 3.3 mm Hg, a prespecified superiority margin (Δ) of 5 mm Hg [22], a one-sided α level of 0.025, and 90% statistical power (1–β). These values were applied to the standard sample size formula for superiority trials to ensure adequate power for detecting a clinically meaningful treatment effect.

### Randomization Method

Allocation concealment was ensured with sequentially numbered, opaque, sealed envelopes. An independent statistician generated the allocation sequence using SAS software (version 9.4; SAS Institute), which assigned participants in a 1:1 ratio to the treatment group (acupoint ST36) or the control group (acupoint GB39). The assignments were sealed in tamper-evident envelopes and stored securely at the coordinating center. Following participant enrollment, the study coordinator retrieved and opened the next sequential envelope to reveal the assignment to the intervention clinician, thereby ensuring complete concealment and unpredictability of the allocation for researchers and participants.

### Blinding

Multiple safeguards were implemented to maintain blinding in this self-administered moxibustion trial. Participants were blinded by being told they “might receive different acupoint treatments” during consent and were assigned only a unique ID. Cross-contact was prevented through segregated scheduling. To ensure consistency and control performance bias, a single clinician (uninvolved in the assessment) provided standardized training to all participants. Data collectors, outcome assessors, and statisticians were blinded, with unblinding permitted only for serious adverse events, which would lead to separate analysis of that participant’s data.

### Intervention Protocol

#### Basic Treatment

After enrollment, participants will continue their previous medication and record it in the case report form.

#### Treatment Group

Participants in the treatment group will receive moxibustion at Zusanli (ST36). All participants will undergo training by professionals on acupoint location, moxibustion techniques, and precautions before beginning treatment. Only patients who pass the training and evaluation will be allowed to perform moxibustion at home, 3 times a week for 12 weeks. The first moxibustion session will be conducted under professional supervision in the clinic, with the skin temperature at the moxibustion site recorded before and after the session. Subsequently, participants will document each moxibustion session with photographs and will complete a moxibustion record form, noting the date, duration, and any adverse reactions. Researchers will conduct 2 random follow-up visits per week to remind participants to complete their moxibustion sessions on time and to verify the frequency, location, duration, and completion of the sessions using photos and record forms. Participants will also undergo outpatient evaluations every 2 weeks to assess their moxibustion adherence and will receive comprehensive assessments at baseline, week 4, week 12, and week 24.

#### Control Group

Participants in the control group will receive moxibustion at Xuanzhong (GB39). The training, evaluation, and assessment procedures will be identical to those of the treatment group to complete the study according to the design process (Figure 1). The time points of the outcome measures are summarized in Table 1.

Acupoint locations in this study are determined according to the “Names and Locations of Acupoints” (GB/T12346-2021) standard (Figure 2).

**Figure 1 figure1:**
[figure not shown]
Flow diagram of the trial procedure. ABPM: ambulatory blood pressure monitoring; FBG: fasting blood glucose; FINS: fasting insulin; HbA1c: glycated hemoglobin; HDL: high-density lipoprotein; LDL: low-density lipoprotein; TC: total cholesterol; MoCA: Montreal Cognitive Assessment.

**Table 1 table1:** Time points of the outcome measures.

Assessment	Enrollment and baseline	Allocation		After allocation						Closeout
		0 wk	2 wk	4 wk	6 wk	8 wk	10 wk	12 wk	24 wk	
Informed consent	✓	—^a^	—	—	—	—	—	—	—	—
Inclusion or exclusion	✓	—	—	—	—	—	—	—	—	—
General information	✓	—	—	—	—	—	—	—	—	—
Random allocation		✓	—	—	—	—	—	—	—	—
Intervention	—	✓	✓	✓	✓	✓	✓	✓		—
Concomitant medication	✓	—	✓	✓	✓	✓	✓	✓	✓	—
24 h ABPM^b^	✓	—	—	✓	—	—	—	✓	✓	—
24 h Holter ECG^c^	✓	—	—	✓	—	—	—	✓	✓	—
Lipid profile (Triglycerides, TC^d^, HDL^e^, and LDL^f^)	✓	—	—	✓	—	—	—	✓	✓	—
Glycemic markers (FPG^g^, FINS^h^, HbA_1c_^i^)	✓	—	—	—	—	—	—	✓	✓	—
^Hepatic and renal function^	✓	—	—	—	—	—	—	✓	✓	—
^Phlegm-damp constitution^	✓	—	—	—	—	—	—	✓	✓	—
Cardiovascular risk stratification	✓	—	—	—	—	—	—	✓	✓	—
MoCA^j^	✓	—	—	—	—	—	—	✓	✓	—
Adverse events and other unintended effects	—	—	✓	✓	✓	✓	✓	✓	✓	—
^Compliance monitoring^	—	—	✓	✓	✓	✓	✓	✓	✓	—
^Completion summary^	—	—	✓	✓	✓	✓	✓	✓	✓	—

^a^Not available.

^b^ABPM: ambulatory blood pressure monitoring.

^c^Holter ECG: Holter electrocardiogram.

^d^TC: total cholesterol.

^e^HDL: high-density lipoprotein.

^f^LDL: low-density lipoprotein.

^g^FBG: fasting blood glucose.

^h^FINS: fasting insulin.

^i^HbA_1c_: glycated hemoglobin.

^j^MoCA: Montreal Cognitive Assessment.

**Figure 2 figure2:**
[figure not shown]
Acupuncture point diagram for the location of the acupoints.

#### Materials and Tools

The material and tools used for moxibustion in this study will include (1) Lei Huo moxibustion device (Registration Number: 20,232,200,237; Hunan Cihui Medical Technology Co, Ltd); (2) OMRON YE-680 series digital blood pressure monitor (Registration Number: 20,202,071,574; Omron Healthcare Co, Ltd); (3) RGT-120/160 weighing scale (Changzhou Wujin Weighing Apparatus Co, Ltd); and (4) 150 cm measuring tape.

### Assessment and Outcomes

#### Overview

Participants will undergo evaluations at weeks 0, 2, 4, 6, 8, 10, 12, and 24 during outpatient visits. Twenty-four-hour ambulatory blood pressure and 24-hour Holter electrocardiogram will be examined at weeks 0, 4, 12, and 24. General information (weight, height, waist circumference, hip circumference, family history, medical history, concomitant medications, and lifestyle behavior), relevant laboratory tests (4 items of lipids, fasting blood glucose, glycosylated hemoglobin, serum insulin, homeostatic model assessment of insulin resistance, homeostatic model assessment of β-cell function, insulin-sensitivity index, triglyceride-glucose index, metabolic score for insulin resistance, liver function, and kidney function), heart function, vascular risk stratification, and scale assessment (TCM phlegm-dampness physique score and the Montreal Cognitive Assessment) will be examined at weeks 0, 12, and 24. Major unconscionable cerebrovascular injury, target organ injury, and moxibustion adverse events will be recorded during the study period.

#### Primary Outcome Measure

In this study, the primary outcome measure is the morning systolic blood pressure, which will be measured by 24-hour ABPM (assessment at weeks 0 and 12).

#### Secondary Outcome Measures

##### Blood Pressure–Related Indicators (Measured by 24-Hour ABPM)

Morning diastolic blood pressure, average systolic blood pressure, average diastolic blood pressure, nighttime systolic blood pressure, nighttime diastolic blood pressure, and circadian rhythm of blood pressure will be assessed (at weeks 0, 4, 12, and 24). Twenty-four-hour diastolic blood pressure, 24-hour nocturnal systolic blood pressure, 24-hour nocturnal diastolic blood pressure, 24-hour morning systolic blood pressure, 24-hour morning diastolic blood pressure, circadian rhythm of blood pressure, 24-hour systolic blood pressure variability, and 24-hour diastolic blood pressure variability will also be assessed at different time points (at weeks 0, 4, 12, and 24)

##### Cardiac-Related Indicators (Measured by 24-Hour Holter Electrocardiogram)

Total heartbeats, myocardial oxygen consumption, average heart rate, heart rate variability (HRV) parameters (ie, percentage of successive NN intervals that differ by more than 50 ms, HRV triangular index, root mean square of successive differences, SD of normal-to-normal [SDNN] intervals, SD of the average normal-to-normal intervals, SDNN index, low-frequency [LF] power, high-frequency [HF] power, and the LF and HF ratio) will be assessed at weeks 0, 4, 12, and 24.

##### Laboratory Tests

Triglycerides, cholesterol, high-density lipoprotein, low-density lipoprotein, fasting blood glucose, glycated hemoglobin, fasting insulin, homeostatic model assessment of insulin resistance, homeostatic model assessment of β-cell function, insulin-sensitivity index, triglyceride-glucose index, metabolic score for insulin resistance, and liver and kidney function will be measured at weeks 0, 12, and 24.

##### Scale Evaluations

The TCM phlegm-dampness constitution score, Montreal Cognitive Assessment will be administered at weeks 0, 12, and 24.

#### Exploratory Outcomes

After enrollment, participants will be stratified based on cardiovascular risk using a general information survey designed according to the “Chinese Guidelines for the Prevention and Treatment of Hypertension” (2018 revision [20]) as in Multimedia Appendix 3.

For participants with abnormal Holter electrocardiogram results (eg, Sokolow-Lyon voltage exceeding 3.8 mV or Cornell product exceeding 244 mV·ms), a comprehensive echocardiogram will be performed.

For participants with elevated low-density lipoprotein levels (ie, above 3.16 mmol/L), carotid ultrasound will be conducted to compare vascular characteristics and plaque changes before and after treatment.

For participants with decreased glomerular filtration rate (ie, <59 mL/min/1.73 m^2^) or mildly elevated serum creatinine (male: >115 μmol/L [>1.3 mg/100 mL]; female: >107 μmol/L [>1.2 mg/100 mL]), microalbuminuria will be assessed.

